#### Clinical Effectiveness

The clinical effectiveness of the treatment will be evaluated using MHDs [36], the NRS [37], the Headache Impact Test (HIT-6) [38,39], the EQ-5D-5L [40], and the EuroQol visual analogue scale (EQ-VAS) [41], with assessments conducted at each study time point: baseline and 6 and 12 weeks. Evidence indicates that increases in MHDs are linked to lower health-related quality of life (HRQOL) and that a reduction in MHDs by ≤4 contributes to improved patient health outcomes [36,42]. Thus, assessing MHDs in this study is crucial for evaluating treatment efficacy. The NRS measures overall pain intensity and discomfort associated with headache, with patients rating their pain on a scale from 0 (no pain) to 10 (worst pain imaginable) [37,43].

The HIT-6 is a widely used validated tool designed to measure the impact of headaches on a patient’s ability to function normally in daily life, comprising 6 items, each with 5 graded response options [38,39]. Each response is assigned a score ranging from 6 to 13 points per item, resulting in total scores that range from 36 to 78, with higher scores indicating greater impact or burden of headaches [44]. The patients’ HRQOL will be evaluated using the Korean version of the EQ-5D-5L [45]. The EQ-5D-5L assesses HRQOL across 5 dimensions: mobility, self-care, usual activities, pain and discomfort, and anxiety and depression [40,46]. The EQ-VAS will be used to measure the patients’ self-perceived health status on a scale from 0 to 100 [41,47]. Higher scores on the EQ-5D-5L and EQ-VAS indicate better HRQOL and overall health, respectively.

#### Cost-Effectiveness

Cost use for both treatments will be comprehensively assessed, including direct medical costs, direct nonmedical costs, and indirect costs such as productivity losses, derived from CRFs and hospital administrative data. The cost-effectiveness of the treatments will be evaluated using several measures: cost per quality-adjusted life year (QALY) [48,49], the incremental cost-effectiveness ratio (ICER) [50], and the cost-effectiveness acceptability curve (CEAC) [51]. The cost per QALY will be estimated using the area under the curve method [48,52] based on utility scores captured through the EQ-5D-5L and EQ-VAS. The ICER, representing the economic value of collaborative treatment compared with UC, is determined by dividing the incremental cost by the incremental QALYs gained [50,53]. The CEAC illustrates the probability that a treatment is cost-effective across a range of willingness-to-pay thresholds per QALY, with the horizontal axis denoting willingness-to-pay values and the vertical axis representing the corresponding probabilities [51,54].

### Safety

This study establishes standardized guidelines for reporting adverse events during the study period. All abnormal symptoms, adverse effects, or illnesses occurring in participants—regardless of their relation to the treatment received—will be documented. Recorded data will include a description of the event, time of onset, severity assessment by the practitioner, and relationship to the treatment. The research team will assess participant eligibility and determine the need for withdrawal. Additional visits may be scheduled for further evaluation. For participants who withdraw, the reasons will be documented, assessed, and followed up on accordingly.

### Statistical Analyses

Baseline data will be summarized using descriptive statistics such as percentages, frequencies, and means and SDs for both the UC and collaborative treatment groups. The UC group refers to participants receiving treatment exclusively with either KM or WM, whereas the collaborative treatment group includes those receiving both KM and WM. Data normality will be evaluated using the Shapiro-Wilk test and *Q*-*Q* plots. Between-group differences will be assessed using chi-square tests (Fisher exact test) for categorical data and the 2-tailed Student *t* test or ANOVA for continuous data. When normality or equal variance assumptions are violated, the Mann-Whitney *U* test and Kruskal-Wallis test will be performed.

Per-protocol and intention-to-treat (ITT) analyses will be conducted to assess clinical effectiveness and cost-effectiveness. To establish the ITT dataset, the proportion and mechanism of missing data will be evaluated using the Little test. If the data are identified as missing completely at random or missing at random, as defined by Rubin [55], multiple imputation will be performed [55,56]. Mean changes in clinical outcomes over time will be compared between groups as part of the effectiveness analysis. Furthermore, a generalized linear mixed model will be used to assess between-group effects at each time point. To rigorously control for heterogeneity and potential confounders, the model will adjust for fixed effects, including age, sex, headache history (onset duration), specific diagnosis, and comorbidities. While specific treatment modalities vary, reflecting real-world practice, the analysis adheres to the ITT principle to evaluate the effectiveness of the collaborative treatment strategy compared to UC rather than the efficacy of individual modalities. Subgroup analyses will be performed according to headache type (migraine, TTH, or other) and headache severity (episodic or chronic).

Utility values from the EQ-5D-5L and EQ-VAS will be used to estimate QALYs using the area under the curve method [48]. Deterministic analyses for the ICER will be performed using both ITT and per-protocol data from a limited societal perspective and a societal perspective. A probabilistic sensitivity analysis will also be carried out using parameter distributions and estimates. To account for sampling uncertainty in the ICER point estimates, 95% CIs will be calculated using the bootstrapping method or a seemingly unrelated regression model. All statistical analyses will be conducted using Stata/MP (version 14.0; StataCorp) and SAS (version 9.4; SAS Institute), with the significance level set at a *P* value of <.05.

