### Participants and Treatments

The study participants comprise patients diagnosed with primary headache disorders who visit hospitals participating in the fifth phase of the collaborative treatment pilot project and receive either collaborative treatment or UC alone [28]. Patients receiving UC are those treated exclusively with either KM or WM, whereas collaborative treatment refers to treatment involving both KM and WM. To minimize treatment heterogeneity and ensure clinical rigor, the therapeutic procedures for both WM and KM are conducted in strict accordance with the standard clinical practice guidelines (CPGs) for headaches in South Korea [10,33,34]. Specifically, following these standard CPGs, WM interventions typically involve acute abortive medications (eg, nonsteroidal anti-inflammatory drugs and triptans) and prophylactic agents (eg, β-blockers, anticonvulsants, and antidepressants) tailored to the specific headache disorder. Similarly, KM interventions are standardized to include acupuncture, electroacupuncture, pharmacopuncture (herbal injection), chuna manual therapy, and herbal prescriptions as outlined in the corresponding CPGs. In the collaborative treatment group, these standardized modalities are integrated to maximize therapeutic synergy; for instance, a patient may receive WM pharmacotherapy for rapid pain relief concurrently with KM acupuncture or chuna therapy to relieve muscle tension and address functional imbalances. Conversely, the UC group receives monodisciplinary care consisting exclusively of either WM or KM modalities. To ensure consistency across multiple centers, all participating practitioners will undergo standardized training on the study protocol and clinical guidelines before study initiation. Furthermore, adherence to these treatment standards will be periodically monitored by the Monitoring Center for Korean Medicine and Western Medicine Collaboration (MCMC) throughout the study period.

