A nonrandomized observational design was adopted to reflect real-world clinical settings where patient preference acts as a crucial determinant of treatment adherence and outcomes. Consequently, participants will exercise informed choice regarding their treatment modality. During the consultation, practitioners will provide comprehensive information on the expected benefits, potential side effects, and cost implications of both collaborative treatment and UC. On the basis of this shared decision-making process, patients will select their preferred treatment group, ensuring that the study findings mirror actual health care use patterns in South Korea. If a participant opts for collaborative treatment, one practitioner will initiate a collaborative treatment request to the other practitioner. Treatment choices can be adjusted at any time through consultation with practitioners, and all treatments will be recorded and monitored. Patients who agree to participate will be given detailed information about the study and all safety-related aspects before they provide informed consent. After obtaining written consent, a medical doctor or a KM doctor will assess the participant’s eligibility. Those who meet the inclusion criteria will be enrolled in the study and assigned an enrollment number to preserve anonymity. To ensure fair and open participation, announcements about the study will be made publicly available at the participating institutions.

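### Groups are defined by treatment received while patients may switch freely, which conflicts with the stated ITT principle and leaves open which arm a switcher is analysed in

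*Protocol article*

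**What the plan says.** Three strands of the protocol article bear on who belongs to which arm.

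- **Definition.** Participants and Treatments states: "Patients receiving UC are those treated exclusively with either KM or WM, whereas collaborative treatment refers to treatment involving both KM and WM". Statistical Analyses repeats it for the analysis: "The UC group refers to participants receiving treatment exclusively with either KM or WM". For the other arm, the same section says that "the collaborative treatment group includes those receiving both KM and WM". Both definitions rest on what is received, and neither names a time point.
- **Entry and switching.** Participants and Treatments says that, after shared decision-making at the consultation, "patients will select their preferred treatment group". It then adds: "Treatment choices can be adjusted at any time through consultation with practitioners, and all treatments will be recorded and monitored".
- **Analysis principle.** ITT and per-protocol analyses are planned for both clinical and economic outcomes, and "the analysis adheres to the ITT principle to evaluate the effectiveness of the collaborative treatment strategy compared to UC". The ITT dataset is described only through the handling of missing data. The ITT principle is invoked only to justify pooling varied modalities. Neither statement says where a patient who changes treatment is counted.

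**The concern.** Under ITT, a patient stays in the group fixed at the start, whatever happens later. A group defined by exclusive receipt of one discipline can only be determined at the end of follow-up. With switching allowed throughout the 12 weeks, the receipt definition and the ITT principle cannot both be applied to a usual-care patient who adds the second discipline.

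If the receipt definition is used, membership of an arm can depend on how the patient fared after baseline. The weeks before the second discipline began would also be credited to collaboration. The adjustment variables named for the mixed model (age, sex, onset duration, diagnosis, comorbidities) are baseline characteristics and cannot correct for that. The ICER is computed from the same ITT and per-protocol data, so QALYs and costs would be assigned to arms in the same way.

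**Working it through.** **Step 1. Follow individual patients through the two readings.**

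| Patient | Group by treatment received | Group by choice at consultation |
|---|---|---|
| Starts with one discipline, stays with it | UC | UC |
| Starts with one discipline, adds the other at week 5 | Collaborative | UC |
| Starts collaborative, later drops one discipline | Collaborative (has received both) | Collaborative |
| Chooses collaborative, never receives the second discipline | UC | Collaborative |

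Rows 2 and 4 change arm with the reading. Row 2 is the case created by the freedom to adjust treatment.

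**Step 2. Inputs for an illustration of size.**

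- From Sample Size Estimation: pilot NRS 1.85 (SD 1.66) and 2.48 (SD 2.13). The difference is 2.48 − 1.85 = 0.63. With equal weights, SD = √((1.66² + 2.13²)/2) = √3.646 = 1.91. The article does not say which pilot group was collaborative; I take it to be the lower one.
- The stated total is 312 with 10% discontinuation: 312 × 0.9 / 2 ≈ 140 evaluable per group if the split is 1:1 (not stated). Recomputing the sample size with SD 1.91 gives 145 to 146 per group and 323 to 326 in total. That small gap has no bearing here, and 140 per group is used below.
- Assumed, because the article gives none of them: switching rate, reason for switching, and correlation r between week-6 and week-12 NRS.

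**Step 3. Strict selection, no true effect.** Suppose the worst fraction f of UC starters on week-6 NRS add the other discipline, the addition itself has no effect, and they are counted as collaborative. Their mean week-6 excess is m = φ(z_f)/f SDs, so their mean week-12 excess is r × m × 1.91. Regrouping over 140(1+f) and 140(1−f) patients gives

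difference (collaborative − UC) = r × m × 1.91 × 2f/(1 − f²)

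- f = 0.20: m = 1.400, 2f/(1 − f²) = 0.4167. r = 0.4 gives 0.4 × 1.400 × 1.91 × 0.4167 = **+0.45**; r = 0.6 gives **+0.67**.
- f = 0.10: m = 1.755, 2f/(1 − f²) = 0.2020. r = 0.4 gives **+0.27**; r = 0.6 gives **+0.41**.

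**Step 4. Softer selection, by simulation.** Assumptions: 1:1 initial choice, SD 1.9, r = 0.6, probability of switching rising with week-6 NRS (logistic slope 1 to 2 per SD), no effect of the switch itself. The ranges below run over the two slopes.

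| UC starters switching | Shift under the null, by receipt | Contrast by receipt if the true difference is −0.63 |
|---|---|---|
| 5% | +0.10 to +0.17 | −0.50 to −0.44 |
| 10% | +0.19 to +0.30 | −0.38 to −0.28 |
| 20% | +0.33 to +0.49 | −0.20 to −0.03 |
| 30% | +0.45 to +0.66 | −0.04 to +0.17 |

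Grouping by initial choice returned 0.00 and −0.63 throughout, within simulation error.

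**Step 5. Switching unrelated to response.** The shift under the null is zero. A true −0.63 is only diluted, to −0.63/(1+f): −0.60 at 5%, −0.57 at 10%, −0.52 at 20% and −0.48 at 30%. The simulation agrees.

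**Step 6. Consequence for power.** At 140 per group and SD 1.91, power is 79% for 0.63. For the step 4 contrasts it falls to 39% (0.38) and 23% (0.28) at 10% switching, and to 14% at most at 20%. This ignores the slight imbalance that reclassification creates.

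**The case against.** The strongest reply is that the plan already intends groups fixed by initial choice. Patients select a group at the consultation, a collaborative request is then initiated, Table 1 has a combined column for baseline and allocation, the Results section lists treatment preferences among the baseline data, and separate ITT and per-protocol datasets make most sense if the group is set first and adherence judged later. On this view the receipt wording merely describes the two kinds of care, and adjusting a treatment choice need not mean changing group. A condensed article may also leave the rule for switchers to the full protocol or SAP.

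Much of this stands. A reader might infer that the analysis labelled ITT simply is as-treated and that it places usual-care non-responders in the collaborative arm. The article does not support that: it nowhere says that switchers are reclassified or that they are the patients who did poorly.

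It does not dispose of the point, though. A missing detail on switchers would be no finding. Here the article states a membership rule in the analysis section and also states an analysis principle with which that rule is incompatible once switching is free. The sentences on choice at the consultation show that a second reading exists; they do not say which one governs the analysis.

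The figures are also fairly open to challenge. Strict selection of the worst responders is close to a worst case, and the bias shown runs against collaborative treatment, so in these illustrations it would hide a clinical benefit rather than manufacture one.

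**Conclusion.** The point holds as a contradiction in the text. Defining groups by treatment received, allowing changes at any time and claiming ITT cannot all be honoured for a patient who adds a discipline, and the two available readings assign that patient to different arms of the clinical and cost-effectiveness comparisons.

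The size is illustrative only. If switching is driven by poor response and groups follow receipt, 10 to 20% switching shifts the week-12 NRS difference by about 0.2 to 0.7 point against collaborative treatment, compared with the 0.63 used for planning. This rests on assumed switching rates, correlations of 0.4 to 0.6, assumed selection, 1:1 choice and no benefit from the switch itself. If switching is unrelated to response, only dilution remains. The effect on costs was not quantified.

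A reader might also object to combining KM-only and WM-only care in one comparator. That comparator is declared openly and consistently, and it is not part of this point.

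**What to change.** In Statistical Analyses, replace the receipt-based definition with one anchored in time:

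- The ITT group is the treatment group the patient chose at the baseline consultation. Every patient stays in it for clinical outcomes, QALYs and costs, whatever is received later.
- The per-protocol set is the patients who adhered to that choice.
- Any grouping by treatment received is a separate analysis, labelled as-treated.

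Align the wording in Participants and Treatments, so that exclusive or joint receipt describes the care and does not determine arm membership. The freedom to adjust treatment is untouched.

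The cost is a change of text. Treatment preferences are collected at baseline and all treatments are recorded, so no new patients or assessments are needed. The change should be made before outcomes are examined by group; data collection is expected to run to December 2027. The one downside is some dilution when usual-care patients cross over, but that belongs to the strategy effect the plan says it evaluates.

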### Sample Size Estimation

To determine the appropriate sample size, we referenced data from our preceding pilot study, which was a multicenter prospective observational study conducted across 5 medical institutions during the fourth phase of the national collaborative treatment pilot project (December 2023-December 2024). This pilot study aimed to assess the feasibility and preliminary clinical effectiveness of collaborative treatment versus UC in patients with migraine (*ICD-10* code G43) and other headache syndromes (*ICD-10* code G44; Clinical Research Information Service registration KCT0010198). On the basis of the analysis of 59 participants from this pilot study, the NRS values were derived (group 1: mean 1.85, SD 1.66; group 2: mean 2.48, SD 2.13). Using the G*Power program with a 2-sided significance level of .05 and power of 80% (α=.05) and adjusting for a 10% discontinuation rate, the total required sample size for the study was determined to be 312 participants.

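### Multiple imputation for the ITT dataset depends on the Little test identifying MCAR or MAR, which that test cannot do, so the rule cannot be applied as written

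*Protocol article*

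**What the plan says.** The protocol article, Statistical Analyses, sets out a rule in three steps.

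- Scope: "Per-protocol and intention-to-treat (ITT) analyses will be conducted to assess clinical effectiveness and cost-effectiveness".
- Diagnostic, given as the way to establish the ITT dataset: "the proportion and mechanism of missing data will be evaluated using the Little test".
- Condition and action: "If the data are identified as missing completely at random or missing at random", then "multiple imputation will be performed".

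No other means of recognising MAR is named, and nothing is said about what happens if the condition is not met. The same section compares mean changes between groups and adds that "a generalized linear mixed model will be used to assess between-group effects at each time point". QALYs are to be computed by the area under the curve from utilities at baseline, 6 and 12 weeks. The sample size allows for loss by "adjusting for a 10% discontinuation rate".

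**The concern.** The rule treats a hypothesis test of MCAR as a classifier of mechanisms. Of the two conditions that trigger imputation, the test can never affirm one (MAR) and can only fail to reject the other (MCAR). This leaves two problems.

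1. After a rejection the analyst has no valid basis in the text for declaring MAR and no stated alternative. Either the ITT dataset does not exist, or someone decides the mechanism with the outcome data in view.
2. After a non-rejection imputation goes ahead as though the test had confirmed what imputation needs, although MNAR dropout can leave no trace in the observed data.

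The gate governs the ITT versions of both the clinical and the economic results. Participants choose their own treatment and may change it, so dropout related to response is plausible, though the article gives no data on it.

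**Working it through.** No figure in the plan bears on this rule, so there is none to reproduce. The check is a logical one with a numerical illustration.

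**Logic.** The null hypothesis is MCAR.

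| Test result | Compatible with | Can imputation under MAR be justified by the test? |
|---|---|---|
| Reject | MAR, MNAR | No: the two are not separated |
| Do not reject | MCAR, MAR or MNAR that went undetected | No: MCAR is not established |

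**Inputs from the article.** N = 312 and 10% loss (Sample Size Estimation); three visits at baseline, 6 and 12 weeks (Clinical Effectiveness); pilot values "group 1: mean 1.85, SD 1.66; group 2: mean 2.48, SD 2.13".

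**Assumed, not in the article.** Normal scores with SD 1. Correlations (baseline–6, baseline–12, 6–12 weeks) of 0.4/0.4/0.6 in setting A (600 simulated studies each) and 0.5/0.4/0.6 in setting B (800 each). Only week 12 is missing, with logit P(missing) = a + b·z, where a is set to give 10% missing and b is the slope per SD. Test level 5%.

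**Statistic.** With two missingness patterns, Little's statistic sums, over patterns, n × (pattern mean − ML mean)′ Σ⁻¹ (pattern mean − ML mean) over the observed variables. The degrees of freedom are 3 + 2 − 3 = 2. In effect it compares the baseline and 6-week means of patients with and without a week-12 value.

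**Rejection rates at 10% missing.**

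| Slope b | MAR: z = 6-week score | MNAR: z = 12-week score itself (A) | MNAR: z = part of week 12 not predicted by earlier visits |
|---|---|---|---|
| 0.25 | 22% (A) | 10% | all slopes: 4–7% (A) |
| 0.5 | 63% (A), 66% (B) | 28% | 5% (B) |
| 1.0 | 99.5% (A and B) | 78% | 4% (B) |
| 1.5 | 100% (A) | 96% | |

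Under MCAR, setting B rejects in 6%, close to the nominal level. The last column is also nominal for a structural reason: that residual is unrelated to the earlier visits, which are all that the test can compare. The second and third columns show that rejection is common under both MAR and one form of MNAR, so it does not tell them apart.

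**Bias in the single-arm week-12 mean at 10% missing.**

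- MAR: the completer mean is off by 0.01 to 0.08 SD (A, slopes 0.25 to 1.5) or 0.03 to 0.06 SD (B, slopes 0.5 and 1.0). The MAR-based maximum-likelihood mean, standing in for multiple imputation, is within 0.002 SD of the truth (B).
- MNAR through the unpredicted part: the MAR-based mean is off by 0.04 to 0.07 SD (B, slopes 0.5 and 1.0), no better than completers.

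**On the NRS scale.** Pooled SD = √[(1.66² + 2.13²)/2] = √[(2.756 + 4.537)/2] = 1.91. If the pilot SDs apply to the week-12 score, 0.08 × 1.91 = 0.15 points.

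**QALYs.** By the trapezium rule, QALY = (6/52) × [(u₀ + u₆)/2 + (u₆ + u₁₂)/2]. A patient without u₁₂ has no QALY unless it is imputed.

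**The case against.** Several points on the other side are sound.

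- A reader might infer that the rule withholds imputation under MAR, or that a rejection sends the analysis back to completers. The text does not say so. It expressly includes MAR among the conditions for imputing, and it is silent on what follows a rejection. An analyst who rejects MCAR and then assumes MAR acts within its words. What stands is narrower: the text makes that step depend on an identification its named test cannot supply.
- A reader might infer that all effectiveness results hang on the gate. A mixed model fitted by likelihood to all available records is valid under MAR without imputation, so that analysis is less affected.
- A reader might take a near-certain rejection under MAR as the size of the problem. That holds only for steep assumed slopes; at 0.25 per SD the rate is 22%.
- Nor would a rejection show that dropout follows observed outcomes under MAR, since it is equally compatible with MNAR.
- If dropout acts alike in both arms, most of the single-arm bias cancels from the difference.
- Removing the gate does not itself cure MNAR. The lack of a stated MNAR analysis could be left to a full analysis plan and is not the finding here.

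The defence that this is mere condensation does not stand. The article fixes a diagnostic, a condition and an action. A fuller plan could add detail, but it would have to replace this condition to make it workable.

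**Conclusion.** The rule is stated wrongly and should be changed before analysis. The logical defect needs no assumption: the Little test can neither affirm MAR nor exclude MNAR, so the trigger cannot be applied as written and a rejection leaves the ITT dataset undefined or open to a data-driven choice. The rejection rates rest on the assumed correlations, slopes and missingness pattern, and should be read as a range. The likely numerical effect at 10% loss is modest and would grow with more loss: at 20% missing, the setting B errors become 0.06 to 0.11 SD for completers under MAR and 0.08 to 0.14 SD for the MAR-based mean under MNAR. The results most exposed are the mean-change comparisons, QALYs, costs and ICER. This is a point that should be corrected, not one that invalidates the study.

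**What to change.** Remove the Little-test condition. State MAR as the primary assumption and perform multiple imputation whatever the test shows, by treatment group, with baseline and 6-week outcomes, costs and the model covariates as predictors. Add a delta-adjusted MNAR sensitivity analysis that shifts the imputed outcome, utility and cost values. The Little test may still be reported, as description only. The cost is a change of wording and a small amount of extra programming and analysis. No new data are needed, and data collection is expected to run to December 2027, so the change can be made before the analysis.

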**Methods:**

This prospective, 2-arm, multicenter observational study will assess and compare the clinical effectiveness and economic value of collaborative treatment versus UC alone for patients with primary headache disorders. Adults aged ≥19 years with a primary diagnosis of primary headache disorders visiting participating hospitals under South Korea’s national collaborative treatment pilot project will be enrolled. Participants will receive either collaborative treatment (integrating WM pharmacotherapy with KM therapies such as acupuncture, pharmacopuncture, and herbal medicine) or UC (monodisciplinary care with WM or KM alone) based on informed choice. Clinical and cost-related outcomes will be assessed at baseline and 6 and 12 weeks. Clinical outcomes include monthly headache days, the numeric rating scale, the Headache Impact Test, the EQ-5D-5L, and the EuroQol visual analogue scale. The cost-effectiveness evaluation includes the cost per quality-adjusted life year, the incremental cost-effectiveness ratio, and the cost-effectiveness acceptability curve. Both intention-to-treat and per-protocol analyses will be performed.

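### EQ-VAS is named as a source of utility values for QALYs, although the protocol describes it only as a 0 to 100 self-rating of health

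*Protocol article*

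**What the plan says.** Three sections of the protocol article bear on this.

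- **Statistical Analyses**, on how QALYs are obtained: "Utility values from the EQ-5D-5L and EQ-VAS will be used to estimate QALYs using the area under the curve method".
- **Cost-Effectiveness** (under Measures) gives the same plan. The area-under-the-curve estimate is "based on utility scores captured through the EQ-5D-5L and EQ-VAS". The ICER "is determined by dividing the incremental cost by the incremental QALYs gained", and the acceptability curve is plotted against willingness to pay per QALY.
- **Clinical Effectiveness** (under Measures) says what each instrument measures. "The EQ-5D-5L assesses HRQOL across 5 dimensions", and separately, "The EQ-VAS will be used to measure the patients’ self-perceived health status on a scale from 0 to 100". The section then reads higher EQ-5D-5L scores as better quality of life and higher EQ-VAS scores as better overall health.

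The analysis sets and perspectives for the economic evaluation are also given: "Deterministic analyses for the ICER will be performed using both ITT and per-protocol data from a limited societal perspective and a societal perspective". The assessment times are baseline, 6 weeks and 12 weeks (Abstract, Methods).

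**The concern.** A QALY weight has to sit on a scale anchored at 0 for dead and 1 for full health, and it has to reflect how strongly health states are preferred. The EQ-5D-5L can supply such a weight once its five-dimension profile is converted to an index with a value set. The EQ-VAS, as the article describes it, is the patient's own rating of current health. Dividing it by 100 changes its range but adds neither the anchor nor the preference weighting.

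The article nevertheless calls both instruments sources of utility, in two separate sections, so this is a stated method and not a slip of wording.

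The Introduction makes cost-efficiency part of the primary objective, and the conclusions section expects the findings to inform insurance reimbursement. If EQ-VAS enters the denominator of the ICER, the result is no longer a cost per QALY, and willingness-to-pay values expressed per QALY cannot be applied to it.

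**Working it through.** **The plan's own figures.** The article states no QALY, ICER or expected utility gain, so there is nothing to reproduce on this point. The one design figure, 312 participants, rests on NRS values and does not depend on how QALYs are formed.

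**Step 1: the sections side by side.**

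| Section | Role given to EQ-VAS |
|---|---|
| Clinical Effectiveness | Rating of own health, 0 to 100 |
| Cost-Effectiveness | Source of utility scores for the area under the curve |
| Statistical Analyses | Source of utility values for QALYs |
| Results | Listed with EQ-5D-5L as a quality-of-life outcome |

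The second and third rows need a property that the first row does not give. No section describes a weighting, rescaling or anchoring that would supply it.

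**Step 2: both possible readings.** The article does not say how the two instruments are used together.

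- If they are analysed separately, the EQ-VAS version of the ICER has a denominator that is not in QALYs.
- If they are combined, the single denominator contains a component that is not a utility.

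The defect is present either way.

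**Step 3: size of the denominator.** Follow-up is 12 weeks, so a person in full health throughout accrues 12/52 = 0.231 QALY. Between-group differences can only be a fraction of that.

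**Step 4: how the ICER depends on the instrument.** Let the between-group difference in the weight be b at baseline, g1 at week 6 and g2 at week 12. The trapezoidal difference in area, in years, is

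(6/52)(b + g1)/2 + (6/52)(g1 + g2)/2 = 3(b + 2·g1 + g2)/52.

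With no baseline difference (b = 0) and a constant gain g at both visits, this is 9g/52. With incremental cost C, the ICER is C ÷ (9g/52), which is inversely proportional to g.

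**Step 5: illustration.** The cost and gains below are assumptions, not from the documents: C = KRW 200,000 and g from 0.02 to 0.10.

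| Gain g | 9g/52 | C ÷ (9g/52) |
|---|---|---|
| 0.02 | 0.0035 | KRW 57.8 million |
| 0.04 | 0.0069 | KRW 28.9 million |
| 0.10 | 0.0173 | KRW 11.6 million |

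The table has no built-in direction. If EQ-VAS/100 (itself an assumed rescaling) gained 0.10 and the index 0.04, the EQ-VAS figure would be the lower by a factor of 0.10/0.04 = 2.5. With the gains swapped, it would be the higher by the same factor. With equal gains the two would coincide numerically, but the EQ-VAS figure would still not be a cost per QALY.

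**The case against.** The strongest defence is that the article condenses a fuller protocol and that the statistical analysis plan is not shown. Which instrument is the base case, which value set is applied and how scores are rescaled are details commonly left there. Some analysts also report VAS-weighted results as a supplementary analysis, and the article fixes no single threshold that such a result would pass or fail.

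Much of this stands. The absence of a base-case rule and of a named value set is not counted as a fault here. A VAS-weighted analysis may also remain if it is labelled for what it is. What the defence does not remove is the positive statement, made twice, that EQ-VAS yields utilities for QALYs. A later document could limit the use of that statement but would not make it correct. Neither section presents EQ-VAS as a sensitivity analysis. And although no single threshold is set, the acceptability curve's horizontal axis is per QALY, which presupposes a true QALY.

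Three stronger readings are tempting, and the documents do not support them.

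- **Competing ICERs of equal rank.** A reader might infer this, and count up to 2 instruments × 2 datasets × 2 perspectives = 8 deterministic ICERs. But the article speaks of the ICER in the singular, does not say that the instruments are analysed separately, and does not rank them by naming them in one sentence.
- **A bias in favour of collaborative treatment.** A reader might infer that EQ-VAS would make it look more cost-effective by some multiple. Any such multiple only restates the gains assumed, and the direction could be the reverse.
- **Greater exposure of EQ-VAS to expectation.** Treatment is self-chosen, but both instruments are self-reported by the same participants, and nothing in the article separates them in this respect.

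**Conclusion.** The point holds as a stated method that is wrong as written: EQ-VAS is called a source of utility for QALYs, while the article's own description of it does not make it one. Any QALY, ICER or acceptability curve that uses it is not a cost per QALY as the Cost-Effectiveness section defines that quantity.

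The numerical effect is unknown from the documents. What can be said is that the denominator is small and that, at equal cost, the ICER changes in inverse proportion to the gain on the instrument chosen, in either direction. The 9g/52 form assumes equal groups at baseline and a constant gain at both visits. Equal baselines are not assured where patients choose their treatment; the general formula with b covers that case.

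The point is confined to the economic evaluation. Because that evaluation is part of the primary objective, the text should be corrected before analysis.

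**What to change.** Change two places in the article and the matching text of the full protocol or analysis plan.

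1. In **Cost-Effectiveness** and in **Statistical Analyses**, state that QALYs, the ICER and the acceptability curve are based on EQ-5D-5L index values only. The value set can be named there or in the analysis plan.
2. Keep EQ-VAS as the health-status outcome that it already is in Clinical Effectiveness and in Results.
3. If a VAS-weighted economic analysis is kept, label it exploratory or sensitivity, do not call its result a cost per QALY, and do not read it against willingness-to-pay thresholds per QALY.

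The cost is wording. No data collection, assessment time or participant number changes, and the analysis work stays the same or falls. The article reports recruitment still open in December 2025 and data collection running to December 2027, so the change can be made before results are known.
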